### Cost effectiveness

To evaluate cost effectiveness, incremental cost-effectiveness ratios (ICERs) will be calculated [47]. ICERs are calculated by dividing the difference in costs (between the INTV and the CTRL) by the group difference in the outcomes and can be interpreted as the cost to obtain an extra unit of effectiveness, quantifying the trade-offs between patient outcomes gained and resources spend [47]. In our analysis, ICERs will be calculated for primary outcomes (e.g., *motor performance; SPPB total score*) and secondary outcomes (e.g., *health-related quality of life; EQ-5D questionnaire*). Therefore, average costs of the exercise interventions (e.g., training material, visits by trainer, phone calls) as well as overall health care costs (e.g., general practitioner consultations, inpatient and outpatient care, days in hospital, hours of nursing care, hours of professional domestic help or help by family members/friends) will be collected for INTV and CTRL [48]. Overall health care costs will be assessed retrospectively, covering a period of 12 weeks before T1, T2 and T3, using an established questionnaire (FIMA) [49].

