### Statistical analysis and sample size

An intention to treat analysis will be conducted. We performed an a priori power analysis to determine the sample size necessary to obtain significant effects in PA. Power analysis for PA is difficult to calculate since studies using identical sensor-based physical activity assessments in cognitively-impaired geriatric patients have not been available. Thus, the effect size is based on a study conducting a functional strength training program in 137 institutionalized patients [54]. PA, as assessed by the MTI Actigraph, showed an average increase of PA by 43% in the strength training group compared to a control group (effect size: eta^2^ = 0.18). A priori power analysis was performed using GPower 3.1 software [55]. A repeated measure analysis of co-variance (ANCOVA) design including two groups and two repeated measurements yielded a total sample size of *N* = 101 (α = 0.05; critical F = 2.69). Estimating a drop out of 15%, we will recruit a total of 116 participants. For motor performance, as assessed by the SPPB total score, a pilot study conducted by our research group showed that performance improvements can be achieved using relatively small sample sizes (*N* = 34; large effect size: eta^2^ = 0.22 [56]). Repeated measures ANCOVA will be used to determine effects of the home-based training program on primary and secondary outcomes for effects of intervention (T1-T2) and sustainability of effects (T1-T3). Effect sizes are determined by calculating eta^2^ [57]. All data will be analyzed using SPSS 23.0 (SPSS Inc., Chicago, Ill., USA).

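### Eta squared, version unstated, is the only effect-size measure named for the outcomes; no adjusted between-group difference with a confidence interval is specified

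*Protocol article*

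**What the plan says.** The section on statistical analysis and sample size names the model: "Repeated measures ANCOVA will be used to determine effects of the home-based training program on primary and secondary outcomes", for T1-T2 and for T1-T3. The effect measure follows: "Effect sizes are determined by calculating eta^2^ [57"]. No other effect-size measure is named for these analyses, and neither an adjusted mean difference nor a confidence interval is mentioned. The same section uses eta squared for both planning inputs, again without naming the version: "effect size: eta^2^ = 0.18" for physical activity and "large effect size: eta^2^ = 0.22" for the SPPB pilot.

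The primary outcomes have natural units. The section on primary outcomes gives the SPPB total as 0 to 12 points, and the section on physical activity says durations are recorded in minutes. The section on cost effectiveness works with a raw difference: "ICERs are calculated by dividing the difference in costs (between the INTV and the CTRL) by the group difference in the outcomes", and gives the SPPB total score as an example.

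**The concern.** The trial asks whether training improves motor performance and activity. Eta squared is a share of variance, and for that question it falls short in four ways.

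- **No sign.** Equal benefit and harm give the same value. This matters more because the secondary outcomes mix scales on which a high score is unfavourable (GDS-SF, AES-C, Short-FES-I, FFABQ, TuG time) with scales on which it is favourable (LSA, SPPB sub-tests).
- **No unit.** It cannot be read as SPPB points or minutes, so it cannot be set against a change that matters to patients.
- **No zero under no effect.** A sample value is always positive.
- **No single value for one benefit.** It changes with the version and with the T1-T2 correlation. Two outcomes with the same gain in SD units can then seem to respond differently only because one is more stable over time.

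After a non-significant result, an eta squared without an interval also does not show which benefits remain compatible with the data.

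**Working it through.** **The plan's own figures.** The values 0.18 and 0.22 cannot be recomputed, because neither version nor variances are given. The sample size calculation does not settle the version either. It prints "α = 0.05; critical F = 2.69" and no power. A two-group, two-time design has 1 numerator df and a critical F of about 3.94 near N = 101; a value near 2.69 needs 3 numerator df. That mismatch is a separate matter and is not relied on here.

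**Inputs.** From the article: N = 101, two groups, two measurements. Assumed, because the article gives neither: a true T2 difference d = 0.5 SD with equal baselines and SD 1 at both times, and a T1-T2 correlation r between 0.5 and 0.9.

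**Step 1: value under no effect.** With 1 and N - 2 = 99 df, expected partial eta squared is 1/(N - 1) = 1/100 = 0.010. The 95th percentile is F/(F + 99) with F = 3.94, that is 3.94/102.94 = 0.038.

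**Step 2: value for one fixed benefit.** Per participant, in the group-by-time layout:

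- interaction sum of squares = d²/8 = 0.25/8 = 0.03125
- within-subject error = 1 - r
- total = 2 + 3d²/8 = 2.09375

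Partial eta squared = 0.03125/(0.03125 + 1 - r). Classical eta squared = 0.03125/2.09375 = 0.0149, whatever r is.

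| r | Partial | Classical | Ratio |
|---|---|---|---|
| 0.5 | 0.059 | 0.0149 | 3.9 |
| 0.7 | 0.094 | 0.0149 | 6.3 |
| 0.8 | 0.135 | 0.0149 | 9.0 |
| 0.9 | 0.238 | 0.0149 | 16.0 |

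The gap between versions is therefore about 4-fold to 16-fold. Within the partial version, the value grows 0.135/0.059 = 2.3-fold from r = 0.5 to 0.8, and 0.238/0.059 = 4.0-fold from 0.5 to 0.9.

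**Step 3: the same under baseline-adjusted ANCOVA.** Partial eta squared = (d²/4)/(d²/4 + 1 - r²) = 0.0625/(0.0625 + 1 - r²). This gives 0.077, 0.148 and 0.248 at r = 0.5, 0.8 and 0.9: a 1.9-fold change up to 0.8 and a 3.2-fold change up to 0.9.

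**Step 4: reading the planning value backwards.** If 0.18 is a partial interaction value, d = √(8(1 - r) × 0.18/0.82), which is 0.94, 0.59 or 0.42 SD at r = 0.5, 0.8 or 0.9. One printed eta squared thus covers benefits that differ more than twofold.

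**Step 5: what the alternative delivers.** At N = 101 the 95% half-width of a baseline-adjusted difference is about 1.96 × 2 × √((1 - r²)/101), that is 0.34, 0.28 or 0.23 SD at r = 0.5, 0.7 or 0.8. The article gives no SD, so this cannot be turned into points or minutes.

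**The case against.** The strongest reply is that naming eta squared excludes nothing. A reader might infer that the trial will never say how many SPPB points or active minutes were gained. The text does not support that. Nothing says that means or differences will be left out, the cost-effectiveness ratio requires a group difference in outcomes such as the SPPB total, and the study follows CONSORT. For its source study the article itself puts a natural effect ("showed an average increase of PA by 43% in the strength training group compared to a control group") beside the eta squared. Nor does it say that eta squared will enter the cost-effectiveness ratio. All of this stands.

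A reader might also take 16-fold as the general instability of the measure, or as its upper limit. It is neither. It needs d = 0.5, r = 0.9 and a comparison across versions. At r = 0.9 the ratio is about 19 for d = 0.2 and 12.4 for d = 0.8, and within one version the change is only about 2-fold to 4-fold.

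The reference cited for eta squared may define a version; it is not available here, and the article's text names none. Finally, a condensed article may leave reporting detail to a fuller document. That covers silence, but here a choice is stated: the article names its effect measure. Neither the general CONSORT commitment nor the cost-effectiveness formula makes an adjusted difference with an interval the stated measure. The formula also leaves open whether its difference is adjusted and whether it refers to T2 or T3.

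**Conclusion.** The concern holds in limited form. The article fixes eta squared, version unspecified, as the only named effect-size measure for the primary and secondary outcomes, and specifies no adjusted between-group difference with a confidence interval. The lack of sign and unit, and the positive value under no effect, need no assumption about d or r. The size of the ambiguity does: about 4-fold to 16-fold between versions and about 2-fold to 4-fold within the partial version, for d = 0.5 and r from 0.5 to 0.9. No significance test becomes wrong. What is weak is the stated summary of benefit, which should be corrected because a better one is available from the same models.

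**What to change.** In the section on statistical analysis and sample size, replace the eta squared sentence with wording such as: *The treatment effect is the covariate-adjusted INTV minus CTRL mean difference at T2 and at T3, in the outcome's own unit (SPPB points; minutes of active episodes), with 95% confidence interval and stated direction of benefit. Eta squared is given as a supplementary figure, with its version named.* In the section on cost effectiveness, state that this same difference is the denominator of the ratio, and at which time point.

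The cost is a few lines of text. The estimates and intervals come from the models already planned, so no further data or participants are needed.

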## Discussion

Our study is among the first RCTs to investigate a specifically-tailored home-based training program with low entry barriers in geriatric patients with CI at the transition from a rehabilitation unit to their home environment. The proposed training program may represent a feasible and effective tool to improve motor performance and increase PA in patients with CI, thus fostering a sustained change in patients’ activity behavior. The program requires relatively low supervision and material costs and has the potential to be implemented into existing health care plans. If the program will prove to be effective, it may lower the barrier for post-ward geriatric patients to take up training and exercising. The program may enhance the sustainability of rehabilitation programs by improving medical care of multi-morbid geriatric patients with CI using an innovative therapeutic concept at this vulnerable stage of health care.

Previous home-based training studies showed methodological limitations, e.g., only included sub-groups of patients with CI [27–29] or did not measure key-motor performances as primary endpoints [25, 28] and behavioral aspects in terms of PA have not been investigated in geriatric patients with CI. Only a few studies investigated PA in community-dwelling older adults with CI using questionnaires [17, 18, 21]. Hence, there is a lack of studies in post-ward geriatric patients comprehensively evaluating motor performance and PA. The investigation of training-related effects on motor performance and behavioral changes in terms of enhanced PA requires innovative assessment strategies, including sensor-based as well as questionnaire-based measures. In the presented study we will assess primary outcome measures using well-established, validated tests and complement this approach by additionally registering objective and detailed, sensor-based motor data, a range of psycho-social parameters, such as fear of falling, depression and apathy as well as participants mobility status (life-space), quality of life and cognitive functioning. Applying this comprehensive assessment strategy, we will be able to identify training-related modifications of PA and motor performance based on state-of-the-art sensors and examine their relationship with potentially influencing factors, among others, cognitive status or fear of falling. We regard our assessment as a unique and comprehensive combination of quantitative, qualitative, questionnaire and sensor-based data that - to our knowledge - is not available so far.

One aim of our study is to modify behavior in terms of enhanced PA. Participants need to develop intrinsic motivation and volition to adapt their behavior and to become physically active. So far, only one home-based training study for older adults with CI implemented motivational strategies to increase adherence to physical training, by integrating a goal-oriented and individually-tailored training according to the individual’s needs [22]. However, authors did not describe the specific motivational strategy used and did not show data on the feasibility of the motivational support. Our study is going to address this limitation by integrating a specific motivational strategy for patients with CI. Based on various theoretical frameworks (i.e., TPB, SCogT, and CT) [50–52], we will integrate several behavioral change techniques (i.e., information on consequences, barrier identification, proper instructions, goal setting, review of behavioral goals, self-monitoring, and performance-based feedback [53]) into our intervention to ramp up adherence and to increase PA. To the authors knowledge, such a comprehensive interventional approach aiming at behavioral modifications by using individually-tailored motivational instruments not been implemented and evaluated in a home-based training program for patients with CI at the transition from rehabilitation to their home environment before.

In addition, CI represents a high financial burden for the health care systems in western societies [3]. Limited resources in health care require effective interventions that provide high benefits relative to the costs [58]. The presented home-based training program aims to counteract typical health-related limitations in patients with CI and represents a low budget approach. In line with this, our program may encourage the participants to conduct the training sessions independently at their home environments (i.e., no professional monitoring) to minimize costs for supervision by professional trainers. To our knowledge, our study will be the first to also assess economical aspects of a home-based training program for geriatric patients with CI using established instruments (i.e., FIMA [49]) and analyses (i.e. ICER [47, 48]) to objectively yield potential cost effectiveness of the intervention.

In summary, this trial will provide insight into the effect of a specifically-tailored home-based exercise program in patients with CI on motor performance and behavioral change. The program offers several approaches, e.g., a comprehensive and innovative assessment strategy and the integration of individually-tailored motivational strategies to stimulate behavioral change and increase motor performance, may have the potential to enhance the sustainability of geriatric rehabilitation programs in patients with CI.

## Abbreviations

ADL: Activities of daily living
AES-C: Apathy evaluation scale-clinical version
CI: Cognitive impairment
CoP: Center of pressure
CT: Control theory
CTRL: Control group
deg.: Degrees
EQ-5D: EuroQol - 5 Dimensions
FFABQ: Fear of falling avoidance behavior questionnaire
GDS-SF: Geriatric Depression Scale – Short Form
GPS: Global position system
ICERs: Incremental cost effectiveness ratios
INTV: Intervention group
LSA: Life-space assessment
MMSE: Mini-Mental-State-Examination
PA: Physical activity
RCT: Randomized-controlled trial
SCogT: Social-cognitive theory
Short-FES-I: Short - Falls Efficacy Scale – International
SPPB: Short-Physical-Performance-Battery
TPB: Theory of planned behavior
TuG: Timed up and go
WAIS: Wechsler adult intelligence scale
